#### Secondary end point analysis

*Markers of BG control and management intensity*
*Analysis of the HbA1c data:* These data will form a longitudinal data set, with the measurement of time being gestational age. The number of assessments per patient will vary. Some patients may be lost to follow-up. The correlation between repeated measurements on each patient and the variable number of measurements will be taken into account in the mixed-model analysis. In addition to the repeated measurements of HbA1c, patient covariates—age, haemoglobin at recruitment, BMI, gestation at recruitment and ethnic group—will be included in the model as fixed effects. The results will be reported as a comparison between the two groups of the rate of change of HbA1c with time.*BG analysis:* Other exploratory BG metrics will include:
Overall mean BG for fasting, preprandial and postprandial readings;Percentage of readings ‘on target’ (fasting readings as defined ≥3.5 and ≤5.8 mmol/L and postprandial readings ≥3.5 and ≤7.7 mmol/L) for the first 4 weeks after randomisation and the second 4 weeks after randomisation;The value, and week number after randomisation, of the highest weekly mean BGTime to treatment from recruitment in weeks;Number of dose adjustments of hypoglycaemic drugs;Maximum dose of insulin and/or oral hypoglycaemic therapy (metformin).

*Maternal and fetal outcomes as measured by:*
Gestational age at delivery (and percentage of deliveries before 37 weeks);Birth weight (and percentage of babies with birth weight above 90th centile as per the INTERGROWTH-21st Standards for gestational age and gender);Mode of delivery (vaginal, caesarean, assisted);Perineal trauma (third-degree or fourth-degree perineal tear or tear requiring suturing in the operating room);Incidence of shoulder dystocia/birth injury;Incidence of neonatal hypoglycaemia (defined as a serum BG level of <1.5 mmol/L at any time, or requiring special care baby unit (SCBU) admission for feeding);Incidence of neonatal significant hyperbilirubinaemia (defined as requiring phototherapy indicated by a serum bilirubin level of >200 μmol/L at <35 weeks, >250 μmol/L at 35–36 weeks and >300 μmol/L at ≥37 weeks);Maternal weight gain (adjusted for weeks in trial);Maternal pregnancy-induced hypertension or pre-eclampsia (defined according to the International Society for the Study of Hypertension in Pregnancy (ISSHP) criteria^23^);Admission to higher level of care for mother;Admission to higher level of care for neonate.

*Maternal and neonatal outcome analysis*: An analysis of covariance will be carried out when the outcome variable is continuous. The model will contain the term for randomisation group and baseline covariates. The results of a comparison between the two groups will be reported as a treatment effect with 95% CI. The binary variables will be analysed using logistic regression. The model will contain a term for randomisation group and baseline covariates. The results of a comparison between the two groups will be reported as an OR and a risk difference with 95% CI.

*Participants' attitudes*
Patients' attitudes will be assessed by completion of the Oxford Maternity Diabetes Satisfaction survey. This survey was developed based on several existing satisfaction surveys for diabetes management and was adapted and validated within this population.^20^ Descriptive analysis of the scores will be presented and thematic analysis of free-text comments performed.

*Compliance with the BG monitoring system*: Summary statistics will be calculated to describe the frequency of BG measurements.

An exploratory economic investigation of the TREAT-GDM data will take the form of a detailed cost analysis from an NHS and personal perspective of the healthcare treatment pathways of pregnant women using the digital health intervention and those receiving standard clinic care. For the NHS perspective, the exploratory analysis will aim to identify cost differences between both groups in terms of healthcare resource use during delivery, neonatal care, antenatal clinics, redistribution of time for health professionals and medication and associated titration. Personal care categories will concentrate on estimating travel-related costs. A thorough cost analysis of adopting the digital health intervention at a hospital level will be reported. We will report unit costs, resource use and costs separately between treatment arms as restarted by best practice guidelines.^24^

*Economic analysis*: The statistical analysis used for the exploratory economic analysis will be primarily descriptive, and parametric inferences to detect potential statistical cost differences between arms will be conducted only on identified potential cost drivers in the exploratory analysis. For the latter, mean cost differences will be accompanied by appropriate measures of uncertainty including 95% CIs.

Interim analyses will not be performed, and all analyses will be performed after the end of the study. Analyses will be blinded to allocation group.

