## Introduction

Gestational diabetes mellitus (GDM) is defined by the WHO as ‘carbohydrate intolerance resulting in hyperglycaemia of variable severity with onset or first recognition during pregnancy’.^1^ Maternal hyperglycaemia leads to excess transfer of glucose to the fetus resulting in fetal hyperinsulinaemia. The consequence of this is accelerated fetal growth and large babies, which increases the risk of delivery complications such as shoulder dystocia, birth trauma, the need for caesarean section and increased risk of stillbirth.^2^ Recognising and treating gestational diabetes to achieve tight glycaemic control has been shown in randomised controlled trials to reduce obstetric and fetal complications.^3^
^4^

Blood glucose (BG) metabolism and regulation change rapidly in pregnancy. The development of GDM and its progression to requiring pharmacologic treatment can be difficult to predict accurately. Once a woman is on insulin treatment, rapid upward titration of insulin dose is commonly required to maintain optimal glycaemic control and rarely hypoglycaemic episodes may require reduction in insulin dosages.

In order to detect and respond to these physiological and metabolic changes, women with GDM are commonly reviewed by a hospital-based maternity diabetes team, at frequent and regular intervals—typically every 1–4 weeks. This constitutes a significant burden to the patient of having to attend many additional antenatal clinics and to the health system responsible for care.

In recent years, there has been a widening of GDM screening criteria,^5^ a lowering of diagnostic thresholds,^6^ an increasing proportion of pregnant women who are classed overweight or obese and increasing numbers of women from high-risk ethnic groups. These changes have led to a rise in the prevalence of GDM, from a baseline of around 4% in 2008^5^ predicted to reach over 16% in the UK if the new diagnostic thresholds are widely adopted.^7^ Taking these factors together, current maternity diabetes services are likely to become overwhelmed and provision and funding will be required for rapid expansion of these services.

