## Methods and analysis

### Objectives

The primary objective of this trial is to evaluate the efficacy of monitoring BG in pregnancy using remote glucose monitoring (GDm-health) compared to standard clinic care. Efficacy will be determined by comparing BG control as determined by mean BG readings from recruitment until delivery between the intervention and the control group. The secondary objective will be to compare the two groups for compliance to the allocated BG monitoring regime, maternal and neonatal outcomes, glycaemic control using glycated haemoglobin (HbA1c) and other BG metrics, and patient attitudes to care assessed using a validated questionnaire^20^ and resource use.

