**Figure 3 BMJOPEN2015009702F3:**
[figure not shown]
Study overview.

BG monitoring targets, dietary advice and thresholds for starting medication will be the same for both allocation groups. All women will be asked to test their BG six times a day on at least 3 days of the week, as per the local guideline. This consists of a fasting sample, 1 h post breakfast, pre-lunch, 1 h post lunch, pre-dinner and 1 h post dinner. Optimal BG is a fasting reading ≥3.5 and ≤5.8 mmol/L and 1 h postprandial readings below 7.8 mmol/L.^11^ If there are persistently high BG readings, or medication is deemed to be required, women will be asked to increase monitoring to 7 days/week.

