### Safety

Supervision in the form of weekly meetings with the clinicians, research team and the diabetes midwives will occur to ensure adherence to the protocol and to resolve problems and queries.

The use of self-capillary BG monitoring is well established in the pregnant and non-pregnant population. Safety concerns include adequate alerts if the remote glucose testing groups have either high or low BG readings or are not providing readings. This will be addressed by having automatic alerts activated to ensure abnormal results are not ‘missed’. The equipment to be used is a standardised, approved glucose meter with Bluetooth technology. It has been used in numerous previous studies and found to be robust. Decisions about patient care will continue to be made by trained doctors and midwives. The technology will not be relied on to automatically alert patients or provide automatic changes in management in response to the readings the system receives.

The m-health system uses a standard BG meter (OneTouch UltraEasy, LifeScan, Inc), which connects to a smartphone (HTC Desire C with Android Operating System V.4.1) via a commercially available Bluetooth adapter (Polytel Wireless Glucose Meter Accessory (GMA), Polymap Wireless LLC). The users measure their BG in the same way as usual care, but the GDm-health system allows a copy of the readings to be transmitted to the smartphone via Bluetooth. The readings are then transmitted to a secure NHS server in real time via the mobile phone data network, using checksums and encryption to ensure data integrity. The BG readings are stored in the user's meter, as well as in the smartphone memory and on the NHS server. No patient-identifiable data are transmitted between the meter and the phone or between the phone and the NHS server.

A business continuity plan has been developed to ensure women using the GDm-health system and their healthcare professionals have a contingency plan if the system fails.

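### The exploratory on-target percentage pools readings below 3.5 mmol/L with readings above range, and no other listed outcome isolates maternal low glucose by arm

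*Protocol article*

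**What the plan says.** The Objectives section judges efficacy on an average: "Efficacy will be determined by comparing BG control as determined by mean BG readings from recruitment until delivery".

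The Secondary end point analysis adds exploratory glucose metrics: means by type of reading, the on-target percentage, and "The value, and week number after randomisation, of the highest weekly mean". The on-target ranges are "fasting readings as defined ≥3.5 and ≤5.8 mmol/L and postprandial readings ≥3.5 and ≤7.7 mmol/L) for the first 4 weeks after randomisation", with the same percentage for the second 4 weeks. Treatment markers follow: time to treatment, "Number of dose adjustments of hypoglycaemic drugs", and maximum dose. The maternal and fetal outcomes include neonatal hypoglycaemia and maternal admission to a higher level of care, but no maternal low-glucose outcome.

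The clinical target under Treatment allocation is "Optimal BG is a fasting reading ≥3.5 and ≤5.8 mmol/L and 1 h postprandial readings below 7.8 mmol/L". It has no postprandial floor and no range for pre-lunch or pre-dinner readings. The same section says "BG monitoring targets, dietary advice and thresholds for starting medication will be the same for both allocation groups".

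The Introduction acknowledges, for women on insulin, that "rarely hypoglycaemic episodes may require reduction in insulin dosages". The Safety section lists among its concerns "adequate alerts if the remote glucose testing groups have either high or low BG readings or are not providing readings", and says that automatic alerts will deal with this.

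**The concern.** A lower mean glucose counts as better control in this trial, so readers of a lower mean will ask whether it came with more low readings. The question is reasonable here. The intervention arm has half the clinic visits and receives dose changes remotely between them. The contact triggers described for both arms are all for high readings. Women needing immediate insulin are excluded, but insulin can start later, since its maximum dose is a listed outcome.

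The on-target percentage is the one listed metric that sorts out low readings, and it then merges them with highs. The article also wants to compare glucose metrics so as to choose a primary outcome for a definitive trial (Discussion). A metric that cannot tell lows from highs serves that aim less well than one that can.

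**Working it through.** **1. The plan's own figure.** Inputs from Sample size: SD 0.8 mmol/L, 100 per arm, 80% power, alpha 0.05 (taken as two-sided). Detectable difference = (1.96 + 0.8416) × 0.8 × √(2/100) = 0.317, which matches the stated 0.32. For 0.32, n = 2 × 2.8016² × 0.8² / 0.32² = 98.1, so 99 per arm. Nothing below changes this.

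**2. What each listed outcome can show about maternal lows.**

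| Listed outcome | Isolates lows? |
|---|---|
| Mean glucose, overall and by reading type; HbA1c | No, averages |
| On-target percentage | Has a floor, but lows and highs share one off-target group |
| Highest weekly mean | No, upper end only |
| Dose adjustments | No, a count printed without direction |
| Time to treatment; maximum dose | No |
| Neonatal hypoglycaemia | No, it concerns the baby |
| Maternal admission to higher care | Could catch only severe events, and does not identify their cause |

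**3. Why the percentage cannot separate them.** On target = 100 − below − above. If below rises by s points and above falls by s points, the percentage is unchanged, whatever the starting shares. If below rises and above does not fall, the percentage does drop, but the drop looks the same as one caused by more highs.

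**4. Illustration (all shares and category means assumed).** Category means are 8.5 above, 5.8 in and 3.2 below range (mmol/L).
- Start, 25/74/1% above/in/below: 0.25 × 8.5 + 0.74 × 5.8 + 0.01 × 3.2 = 6.449.
- Two points moved from above to below: 0.23 × 8.5 + 0.74 × 5.8 + 0.03 × 3.2 = 6.343. The on-target share stays at 74%, lows go from 1% to 3%, and the mean falls by 0.106.
- Range over category means: 0.02 × (8.0 − 3.4) = 0.092 to 0.02 × (9.5 − 3.0) = 0.130.
- In readings: 4 of the 6 scheduled daily tests have a range, so 12 of the minimum 18 a week. The swap adds 0.02 × 12 = 0.24 lows per woman per week, or 0.02 × 18 = 0.36 if it applied to all readings.
- Reading the mean beside the percentage does not settle it. If in-range readings alone were lower by 0.106 / 0.74 = 0.14 mmol/L, the mean would fall by the same 0.106 with 74% on target and no extra lows.

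**5. A second illustration (assumed normal fasting readings, limits 3.5 and 5.8).** With SD 0.8, means of 4.85 and 4.45 both give 83.7% on target, with 4.6% and 11.8% of readings below 3.5. Across SDs of 0.6 to 1.0 and means 0.2 to 0.6 either side of the 4.65 midpoint, pairs with equal on-target percentages differ in lows by 4.5 to 25.1 points. This shows what the metric permits; it is not a forecast.

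**6. Could lows drive the primary result?** On the assumed means, lows alone would have to rise by 0.32 / (5.8 − 3.2) = 12.3 points to move the mean by 0.32 (range 0.32/3.2 = 10 to 0.32/2.0 = 16). That is implausible in this population.

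**7. Would a direct summary be informative?** With 100 women per arm and assumed per-woman SDs of 2.2 and 3.9 points, the 95% CI half-width is 1.96 × √((2.2² + 3.9²)/100) = 0.88 points. With SDs of 2.9 and 5.1 it is 1.15, and with 3.6 and 7.0 it is 1.54.

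**The case against.** The strongest reply is that this is table-level detail. The list is exploratory and open-ended, the article is condensed, and the full protocol or SAP may count lows. The metric is also not wrong for its purpose: it measures control against a target, its floor stops lows counting as success, and it stays flat only when extra lows are exactly offset by fewer highs. The dose-adjustment and highest-week metrics were listed for other purposes.

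Most of that stands and sets the weight of the point. It does not remove it, because the on-target definition is printed, and three shares carry everything that one does and more.

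Three stronger readings are tempting but unsupported:
- A reader might take the Safety section to name an excess of lows as a trial concern. It names the adequacy of alerts and says automatic alerts will address it. It does not commit the trial to comparing lows by arm.
- A reader might infer that the postprandial floor was deliberately added, since the clinical target lacks one. The two definitions do differ, but the article gives no reason.
- A reader might conclude that the trial will not report lows at all. The unseen documents may provide for it.

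**Conclusion.** The point holds as a minor safety-reporting weakness. As printed, the only maternal glucose metric with a lower limit does not distinguish lows from highs, and nothing else listed isolates maternal lows by arm. This rests on the wording of the outcome list, not on the illustrations, whose shares, means and SDs are all assumed.

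Any excess of lows is probably small. Targets, dietary advice and medication thresholds are common to both arms, women needing immediate insulin are excluded, and the Introduction calls hypoglycaemic episodes requiring insulin reduction rare. The documents do not support a claim that the primary result is at risk: the primary analysis and sample size are unaffected.

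**What to change.** In Secondary end point analysis, replace the single on-target percentage with three shares by arm for each 4-week window:
- fasting: below 3.5, 3.5 to 5.8, above 5.8 mmol/L;
- postprandial: below 3.5, 3.5 to 7.7, above 7.7 mmol/L.

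Add one descriptive safety summary: for each woman, the percentage of all readings below 3.5 mmol/L from recruitment to delivery. Report the mean by arm and the between-arm difference with a 95% CI (bootstrap over women), without a test. One value per woman is needed because daily testing gives 6 × 7 = 42 readings a week against 6 × 3 = 18. State that applying 3.5 to pre-lunch and pre-dinner readings is a choice and not a clinical definition of hypoglycaemia.

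For the control arm, use the meter readings downloaded at the end of pregnancy (Measures of BG) instead of the transcribed diaries, so that lows are captured comparably with the automatically transferred intervention readings. Meal labels for the three-way split would still come from the diary; the share below 3.5 needs none, because the floor is the same for both types. Give the number of women without usable readings by arm.

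The cost is one changed and one added summary, from readings the plan already collects. No new data, visits or patients are needed.

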### Study design

This is an open-label, individually randomised controlled trial of 200 women who have had an abnormal oral glucose tolerance test (OGTT) in their current pregnancy. Patients are randomised to the intervention (using the GDm-health management system) and half the number of clinic visits or to normal clinic care. Patient participation is from recruitment (a time point in pregnancy between 14 and 34 completed weeks of pregnancy) until delivery.

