### Source and screening of potential participants

Pregnant women found to have GDM will be assessed by a specialist diabetes midwife. All women will be taught how to test and record their BG levels and asked to keep a food diary for 1 week. All women will be given an information leaflet about the study at their first visit. One week later, they will be assessed again in the specialist diabetes midwife clinic. At this visit, women will be given dietary advice and have baseline measurements taken (box 1). Those requiring insulin treatment for their gestational diabetes will start treatment and be referred to the consultant-led antenatal diabetes clinic. Those not requiring pharmacological treatment or only requiring oral hypoglycaemic therapy (metformin or glibenclamide) and that meet the inclusion/exclusion criteria listed in table 1 will be eligible for the trial and invited to participate. Figures 1 and 2 summarise the study selection process.
Box 1Measurements takenThe baseline measures at recruitment:
Gestational age (days)Weight (kg)AgeParityEthnicitySmoking statusHighest education levelHbA1c (%)Medication (type and dosage)Blood pressureOral glucose tolerance test resultMeasures taken at subsequent clinic visits
Glycated haemoglobinChanges to medicationWeight (kg)Maternal and fetal outcomes
Gestational age at delivery (days)Birth weight (kg)Mode of delivery (vaginal, caesarean, assisted)Severe perineal injury (binary)Shoulder dystocia/birth injury (binary)Neonatal hypoglycaemia (binary)Neonatal hyperbilirubinaemia (binary)Diagnosis of maternal pregnancy-induced hypertension or pre-eclampsia (binary)
Admission to higher level of care (maternal) (binary)Admission to higher level of care (neonate) (binary)

**Table 1 BMJOPEN2015009702TB1:** Inclusion and exclusion criteria

Inclusion criteria	Exclusion criteria
An abnormal glucose tolerance test in this pregnancy (as defined by IADPSG recommendations^6^)	Impaired cognitive function such that she is unable to operate m-health equipment
Women not requiring pharmacological treatment at recruitment	Any evidence of fetal compromise
Women started on oral hypoglycaemic therapy at recruitment	Known risk factors for obstetric complications, other than obesity and gestational diabetes
Willing and able to give informed consent for participation in the study	Gestational diabetes requiring immediate insulin treatment
Female aged between 18 and 45 years	Twins or higher order pregnancy

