### Standard clinic care group

Participants in the standard clinic care group will self-record their BG values in a paper diary at home. They will be scheduled to attend the maternity diabetes clinic every 2–4 weeks where a midwife or specialist will review their readings. If, between visits, they have two or more consecutive postprandial readings ≥7.8 mmol/L or fasting readings ≥5.9 mmol/L or one reading above 9.0 mmol/L at any time of day, they will be instructed to leave a phone message for the specialist diabetes midwife. The midwife will return their call and provide further discussion and dietary advice within 72 h. If pharmacological treatment is required, the participants will be referred to the consultant-led diabetic clinic to start treatment.

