### Remote glucose monitoring group

Participants in the intervention group will be given a smartphone with a preinstalled GDm-health application and Bluetooth-enabled BG meter. The research team will teach intervention participants how to use the application (figure 4). Intervention participants will be asked to attend the clinic every 4–8 weeks (ie, half as many clinic visits as the standard care group). Healthcare professionals and participants will have access to different parts of the GDm-health management system. Participants will access the front-end, an Android smartphone application and healthcare professionals will access the back-end, a server hosted within the local Trust NHS network, through a web interface. The system is described in more detail below.

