**Figure 4 BMJOPEN2015009702F4:**
[figure not shown]
The GDm-health Management System.

Participants will be invited to contact the specialist diabetic midwife using a call-back request function in the smartphone application, or by phone call, if they have any concerns. A specialist diabetes midwife will review the results of the remote monitoring at least three times a week. If a participant has two or more consecutive postprandial readings ≥7.8 mmol/L or fasting readings ≥5.9 mmol/L or one reading above 9.0 mmol/L at any time of day, the specialist midwife will call the participant or send an SMS message from the web interface to the participant’'s phone inviting discussion and further dietary advice. If fewer than 12 of the minimum 18 readings a week are being done, an automatic alert will be generated on the web interface for the diabetes specialist midwife. If this alert persists for 2 weeks, the specialist diabetes midwife will contact the participant. If there is evidence that pharmacological treatment is required, the participant will be referred to the consultant-led clinic to start treatment. Further dose adjustments and messages of advice/encouragement will be communicated to the participant between clinic visits via the GDm-health management system by the specialist diabetes midwife.

Measures taken in both groups at subsequent visits and after delivery are listed in box 1.

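### If maternal weight gain is closed by the last clinic weight but adjusted for weeks to delivery, halving the visits would make the remote arm appear to gain less

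*Protocol article*

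**What the plan says.** Under Secondary end point analysis, the maternal and fetal outcomes include "Maternal weight gain (adjusted for weeks in trial"). Continuous outcomes in that list are analysed by analysis of covariance with randomisation group and baseline covariates. The treatment effect is reported with a 95% CI.

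Box 1 (Source and screening of potential participants) gives the measurement times. Weight is a baseline measure, and it is the last item under subsequent clinic visits, just before the delivery outcomes begin: "Glycated haemoglobinChanges to medicationWeight (kg)Maternal and fetal outcomes" (the extracted text runs the list items together). No maternal weight appears among the delivery outcomes. The section on the remote group confirms that the box serves both arms: "Measures taken in both groups at subsequent visits and after delivery are listed in box 1".

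Visit frequency differs by design. Controls are "scheduled to attend the maternity diabetes clinic every 2–4 weeks". For the remote arm, "Intervention participants will be asked to attend the clinic every 4–8 weeks", which the article describes as half as many visits.

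The Study design section says "Patient participation is from recruitment" and ends it at delivery. That is the only definition of time in the trial that the article gives.

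**The concern.** The analysis needs one gain per woman, and so one closing weight. On the measurement list as written, the natural candidate is the weight at the last clinic visit. Because visits are half as frequent in the remote arm, that weight would tend to lie further before delivery there, and more of the late-pregnancy gain would go unrecorded.

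Time from recruitment to delivery is balanced between the arms by randomisation. It says nothing about when the last weight was taken, so dividing by it or adding it as a covariate would leave the difference in weighing windows in place. The distortion would run in one direction, towards less gain with GDm-health. It would come from the visit schedule and not from any effect of the system, and it would be reported as a treatment effect with a confidence interval.

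**Working it through.** **The plan's own figures.** The article states no expected difference or SD for weight gain. Its one sample-size figure concerns mean blood glucose, and it reproduces: 0.8 × √(2/100) × (1.96 + 0.84) = 0.317, against 0.32 mmol/L stated. It has no bearing on weight.

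**Inputs from the article.** Clinic interval 2–4 weeks (control) and 4–8 weeks (remote); follow-up from recruitment to delivery; 100 women per arm.

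**Assumed inputs, not in the article.** Weekly gain 0.2–0.5 kg; SD of gain 3–5 kg; delivery falling at random within a visit interval; no true difference between the arms.

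**Step 1: gap from last weight to delivery.** With visits every L weeks, the mean gap is L/2.
- Control: mid-interval 3 weeks, gap 1.5 weeks.
- Remote: mid-interval 6 weeks, gap 3.0 weeks.
- Difference: 1.5 weeks. It is (4 − 2)/2 = 1.0 at the short ends of the intervals and (8 − 4)/2 = 2.0 at the long ends.

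**Step 2: spurious difference in kg** = difference in gap × weekly gain.
- Lowest: 1.0 × 0.2 = 0.2 kg.
- Middle: 1.5 × 0.3 = 0.45 kg.
- Highest: 2.0 × 0.5 = 1.0 kg.

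**Step 3: simulation with no true effect.** This used 100,000 women per arm, intervals uniform on the stated ranges, recruitment uniform from 14 or from 28 weeks up to 34+6, and delivery at about 39 weeks (SD 1.3). Mean gaps came out at 1.5 and 3.0 weeks. The apparent remote-minus-control differences were:

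| Adjustment | Women included | 0.2 kg/week | 0.3 kg/week | 0.5 kg/week |
|---|---|---|---|---|
| Weeks to delivery | All (no later visit = zero gain) | −0.31 to −0.32 | −0.45 to −0.46 | −0.76 to −0.77 |
| Weeks to delivery | At least one later visit | −0.12 to −0.28 | −0.18 to −0.39 | −0.31 to −0.65 |
| Weeks between the two weights | Either set | −0.019 to −0.005 | −0.003 to +0.003 | −0.010 to −0.003 |

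Each range spans the two recruitment windows. Counting weeks between the two weighings removes the artefact.

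**Step 4: women with no later scheduled visit before delivery.** About 9% of remote women against 1% of controls with recruitment from 14 weeks, and 29% against 2.5% with recruitment from 28 weeks. The later window is realistic, since women without previous GDM have their glucose tolerance test around 28 weeks (The population studied).

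**Step 5: false positive rate.** SE = SD × √(2/100), which is 0.42, 0.57 and 0.71 kg for SD 3, 4 and 5. The two-sided rejection probability at shift b is 1 − Φ(1.96 − b/SE) + Φ(−1.96 − b/SE):

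| SD (kg) | b = 0.2 kg | b = 0.45 kg | b = 1.0 kg |
|---|---|---|---|
| 3 | 7.6% | 18.5% | 65.4% |
| 4 | 6.4% | 12.5% | 42.4% |
| 5 | 5.9% | 9.8% | 29.3% |

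**The case against.** The strongest reply is that two links in the chain are inferred. The article does not say that the gain ends at the last clinic weight, and it does not say that weeks in trial ends at delivery for this outcome. The short parenthesis could be coded as time to the last weight, and then the artefact is about zero.

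Other weights may also exist. Box 1 does not limit clinic visits to the diabetes clinic. The Introduction describes diabetes reviews as additional to other antenatal clinics. Women who need drug treatment are referred to the consultant-led clinic. Clinical data are extracted from the notes and the electronic record (Data handling and record-keeping). Any of these could bring the last weights in the two arms closer together. It can also be said that an article leaves such detail to the full protocol or analysis plan.

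Most of this stands, and it makes the point conditional. It does not remove the point. The article does not merely leave the adjustment open: it names one, and the only definition it gives of time in the trial makes that adjustment unable to do its job. HbA1c is also measured at clinic visits, and for it the article specifies a mixed model on gestational age that allows for a varying number of measurements. Weight gain gets no such treatment.

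A reader might infer that the remote arm will show less weight gain whatever happens. The documents do not support that. It follows only if both inferred readings are the ones applied and no later weights are used.

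**Conclusion.** The point holds conditionally. If the last clinic weight closes the interval and the weeks are counted to delivery, the stated adjustment leaves a one-directional artefact towards less gain in the remote arm. The 1.5-week difference in cut-off (range 1–2) follows from the article's visit intervals, given delivery at random within an interval. The 0.2–1.0 kg rests in addition on an assumed weekly gain, and would shrink with extra visits or weights near delivery. The false positive rate runs from near nominal (5.9% at 0.2 kg, SD 5) to well above 5% (65.4% at 1.0 kg, SD 3), so no single figure should be quoted as the expected error rate. Closing weights would also be missing more often in the remote arm. The primary outcome and the sample size are unaffected. The wording should be changed because the remedy is cheap.

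**What to change.** Replace the weeks-in-trial adjustment for this outcome with adjustment for the weeks between the recruitment weight and the last recorded weight, and state that the last recorded weight closes the interval. Alternatively, analyse all dated weights in a mixed model on gestational age with an arm-by-time term, in line with the HbA1c analysis. Apply the same rule on eligible weights in both arms.

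The cost is one line of endpoint wording, plus extraction of the weighing dates. Box 1 lists weight in kilograms but does not say that the date is captured, so this should be confirmed. Under the simple rate, women with no follow-up weight drop out, and on the stated schedule there would be more of them in the remote arm. The simple rate also assumes a steady weekly gain, as the simulation did. The mixed model largely avoids the first problem and can relax the second, so it is the better choice if the dates are available.
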